**Methods:**

A stepped wedge cluster randomised controlled intervention design will be used in this trial in Oslo, Norway. Paramedics at five ambulance stations will enrol adult patients with suspected stroke within 24 h of symptom onset. All paramedics will begin in a control phase with standard procedures. Through an e-learning program and practical training, a random and sequential switch to the intervention phase takes place. A mobile application for NIHSS scoring, including vital patient information for treatment decisions, transferring data from paramedics to the on-call stroke physician at the Stroke Unit at Oslo University Hospital, will be provided for the intervention.

The primary outcome measure is positive predictive value (PPV) for prehospital identification of patients with acute stroke defined as the proportion of patients accepted for stroke evaluation and discharged with a final stroke diagnosis. One thousand three hundred patients provide a 50% surplus to the 808 patients needed for 80% power to detect a 10% increase in PPV.

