**Fig. 1 Fig1:**
[figure not shown]
Schedule of enrolment, intervention and assessment of ParaNASPP according to SPIRIT guidelines

All five ambulance stations in the city of Oslo are included in the study, each representing an individual cluster for patient recruitment. Between 250 and 300 paramedics working in these five clusters will participate in the study. After an initial 12-week period where all ambulance stations are in the control group, a random and sequential crossover of clusters from control to intervention will take place until all clusters are activated for intervention (Fig. 2). The clusters are activated only after successful completion of mandatory training, in 12-week intervals. For the last interval, all ambulance stations are enrolled in the intervention group. After 72 weeks patient inclusion is ended. The study will be completed after the final patient with a stroke diagnosis has had a 90-day follow-up.

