### Sample size calculation

Local registry data suggest that around 40% of patients admitted with stroke symptoms to the ED at OUH have a stroke diagnosis at discharge (700 stroke diagnoses out of 1800 admitted with suspected stroke during 2017 (unpublished data)). The prehospital pathway is not specified in the historical data. We aim for a 10% increase in the proportion of patients with a stroke diagnosis at discharge.

We used a two-sided test with alpha 5% and beta 80% and need a total of 808 patients to reach statistical significance. Due to the challenges of prehospital research in terms of large natural variation and loss to follow-up, we aim for a 50% patient surplus and intend to include 1300 patients. We estimate a 72-week study period to be sufficient to reach our goal. With all five stations including control patients before a stepwise cross-over to intervention, we end up with six 12-week periods. After the last cross-over, all paramedics have received training in the ParaNASPP model, and inclusion to the control group ends at this point. The study will be terminated after 72 weeks regardless of the number of patients included in the two groups.

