### Statistics

We will present continuous data as mean (standard deviation) for symmetrical data, and median (quartiles) for skewed data. Categorical data will be presented as absolute numbers and percentages. Classical parametric and non-parametric statistical tests will be used to compare differences between the intervention and control groups as appropriate.

PPV will be calculated with 95% confidence intervals (CI) and used for statistical testing and comparison between groups. This comparison will be performed primarily on the total number of patients included, but adjustments for the temporal inclusion design using hierarchical models will also be explored. The stepped wedge design allows for investigation into potential temporal trends, and subgroup analysis will be done to compare PPV (CI) for the various clusters and time periods using appropriate linear and non-linear curve fitting models.

A modified Rankin Scale (mRS) shift analysis to assess discharge and 90-day functional outcomes [25] will be performed. mRS will be analysed both as an ordinal scale (0–6) and as a dichotomised variable where mRS 0-2 defines a favourable outcome. As shown in Table 2, a certain analysis will only be considered for a subgroup population.

Statistical analysis will be performed in Stata and R.

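### The 808 patients for 80% power are a figure for independent patients; once calendar period is adjusted for in this five-station stepped wedge, even 1300 patients fall short of 80%

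*Protocol article*

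**What the plan says.** The Sample size calculation section starts from local registry data in which "around 40% of patients admitted with stroke symptoms to the ED at OUH have a stroke diagnosis at discharge" (700 of 1800). It aims for a 10% increase and uses a two-sided 5% test. It concludes that the investigators "need a total of 808 patients to reach statistical significance". The Abstract (Methods) puts the same claim as "the 808 patients needed for 80% power to detect a 10% increase in PPV" and calls 1300 a 50% surplus over it. The surplus is explained in the Sample size calculation section this way: "Due to the challenges of prehospital research in terms of large natural variation and loss to follow-up".

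The design is a stepped wedge with five ambulance stations as clusters. Under Study design, "a random and sequential crossover of clusters from control to intervention will take place", in 12-week intervals, giving six periods. The Statistics section compares PPV primarily on all included patients pooled, and adds that "adjustments for the temporal inclusion design using hierarchical models will also be explored". Enrolment stops at 72 weeks whatever the number included.

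**The concern.** In a stepped wedge the share of intervention patients rises with calendar time, so treatment and time are partly confounded. Period 1 is all control and period 6 all intervention, and neither offers a comparison of the two conditions within the same period. Patients from one station may also resemble each other. A calculation for two concurrent groups of independent patients contains neither feature, and 808 looks like such a calculation. The surplus is attributed to variation and loss to follow-up, not to the design, while the Missing data section expects no missing primary outcomes.

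At stake is what readers may conclude. Told that the trial exceeds its 80% requirement, they may read a non-significant period-adjusted result as no effect, although a true 10-point gain could easily produce it. Conversely, a significant pooled result may be read as holding at 5% when it does not.

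**Working it through.** **Inputs from the protocol.** Control PPV 0.40; intervention PPV 0.50, because 10% has to be read as 10 points (a relative 10% increase, 40% v 44%, would need 4778 patients); two-sided alpha 0.05; power 80% (the Sample size calculation section prints this as beta, the Abstract as power); 5 stations, 6 periods, one station crossing per step; 1300 patients planned.

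**Assumptions not in the protocol.** Equal station-periods (30 cells); station correlation (ICC) 0 to 0.05; cluster autocorrelation 1 or 0.8; normal approximation; per-patient variance 0.45 × 0.55 = 0.2475.

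**1. Reproducing 808.** Per group, n = [1.96·√(2·0.45·0.55) + 0.8416·√(0.40·0.60 + 0.50·0.50)]² / 0.10² = 387.3, so 776 in total. With continuity correction it is 407.1 per group, about 816 in total. With 38.9% v 48.9% and the correction it is 812. Conversely, 404 per group gives about 82% power. So 808 is within about 1% of the independent-patient figure. No formula is printed, so this origin is inferred from the match.

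**2. Period adjustment at zero station correlation.** The treated shares in the six periods are 0, 0.2, 0.4, 0.6, 0.8 and 1. The mean of p(1−p) is (0 + 0.16 + 0.24 + 0.24 + 0.16 + 0)/6 = 0.1333, against 0.25 for two concurrent equal groups. The variance inflation is 0.25/0.1333 = 1.875.

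- Patients needed: 776 × 1.875 = 1455. The planned allowance is 1300/808 = 1.61, or 1300/776 = 1.675.
- At 1300: SE = √(0.2475/(1300 × 0.1333)) = 0.0378; power = Φ(0.10/0.0378 − 1.96) = 75%.
- At 808: SE = 0.0479; power = 55%.
- Difference detectable with 80% power at 1300: (1.96 + 0.8416) × 0.0378 = 10.6 points.

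**3. Adding station correlation.** Generalised least squares with period effects and a random station effect, plus a station-by-period effect when autocorrelation is 0.8, at 1300 patients:

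| ICC | Inflation (autocorr. 1) | Power | Detectable difference | Inflation (autocorr. 0.8) | Power | Detectable difference |
|---|---|---|---|---|---|---|
| 0 | 1.875 | 75% | 10.6 points | 1.875 | 75% | 10.6 points |
| 0.005 | 2.44 | 64% | 12.1 | 2.46 | 64% | 12.1 |
| 0.01 | 2.66 | 60% | 12.6 | 2.78 | 58% | 12.9 |
| 0.02 | 2.83 | 58% | 13.0 | 3.21 | 53% | 13.9 |
| 0.05 | 2.91 | 57% | 13.2 | 4.10 | 43% | 15.7 |

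At 808 patients, power over ICC 0.005-0.05 is 40-47% with autocorrelation 1 and 33-47% with 0.8.

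**4. The pooled test.** With independent patients and no trend, its power is about 82% at 808 and 95% at 1300, at a true 5% alpha. With station correlation, its actual standard error at 1300 patients exceeds the nominal one by a factor of 1.25 at ICC 0.01 and 1.96 at ICC 0.05. The type I error is then 2Φ(−1.96/1.25) ≈ 12% and 2Φ(−1.96/1.96) ≈ 32%.

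A calendar trend acts separately. The mean period of control cells is (5·1 + 4·2 + 3·3 + 2·4 + 1·5)/15 = 2.33; that of intervention cells is (1·2 + 2·3 + 3·4 + 4·5 + 5·6)/15 = 4.67. A drift of one point per period (assumed) therefore biases the pooled difference by 2.3 points and gives a type I error of about 13.5% at 1300, even at ICC 0.

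**The case against.** The strongest reply is that the sample size matches the analysis the protocol makes primary. The Statistics section tests the pooled patients and only explores hierarchical adjustment; for that test 808 is correctly computed and 1300 is ample. A random-station model without period effects also gives about 91-92% at 1300 for ICC 0.01-0.05. This stands in part. A reader might infer that neither 808 nor 1300 delivers 80% power under any analysis, or that 808 is an arithmetical slip. The protocol supports neither reading. What the reply does not rescue is the stated alpha: the pooled power is power at 5% only if stations do not differ and PPV does not drift. Drift is a live possibility here: the Trial status section reports a pandemic pause of almost seven months, and the training section reports a change of training format between clusters three and four.

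Two further limits are fair. A reader might take 1.875 as the least inflation this schedule can have. It is not a strict bound: with autocorrelation 1, inflation falls to 1.76 at an ICC of 0.45, though such a value is implausible for PPV between stations of one city. And the large shortfalls rest on assumed correlations; the part that needs none is 75% instead of 80%.

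Finally, an article may condense, and an unprinted ICC alone would be no finding. But the article itself asserts the 80% power and the surplus, and those statements need the qualification.

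**Conclusion.** The point holds in conditional form. The figure of 808 is that of an independent-patient comparison and cannot be a period-adjusted requirement for this design, which is about 1455 even at zero station correlation. The published power is valid only for the pooled test with no station correlation and no calendar trend. With period adjustment, 1300 patients give about 75% power at correlation 0, about 57-64% at 0.005-0.05, and down to about 43% with autocorrelation 0.8. The detectable difference is 10.6 points at best and about 12-16 otherwise.

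These results assume equal station-periods and the normal approximation. With only five clusters, a small-sample correction would lower power further. The correlation and autocorrelation ranges are assumptions, not protocol figures.

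**What to change.** In the Abstract and the Sample size calculation section:

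- Label 808 as the number for independent patients, not the requirement of the stepped wedge.
- State the period-adjusted power of 1300 patients in 5 stations × 6 periods over a stated, assumed range of station correlation: about 75% at 0 and about 43-64% at 0.005-0.05, the lower end reflecting autocorrelation 0.8.
- State the difference detectable with 80% power: 10.6 points at best, about 12-16 otherwise.
- Say that these figures belong to the period-adjusted model, and make that model, not the pooled test, the analysis on which the power claim rests. The Statistics section should agree; otherwise the power statement would describe an analysis that is only exploratory.
- Drop the claim that 1300 is a surplus over the number needed for 80% power. In passing, write power 80% for beta 80%, and note that 1300 is 61% above 808, since a 50% surplus would be 1212.

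No extra patients are needed and the conduct of the trial does not change. The cost is rewording and a less favourable stated figure.

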#### Missing data

For the primary endpoint of PPV, there will be no missing data as all patients seen by the stroke team will have a discharge diagnosis of stroke or non-stroke. For missing data in all other categories, data will be attempted obtained through consensus and interpretation based on narrative information in the patient records. The frequency of missing data for each variable will be reported. For data with > 5% missing, multiple imputation will be done to reduce bias.

### Statistics

We will present continuous data as mean (standard deviation) for symmetrical data, and median (quartiles) for skewed data. Categorical data will be presented as absolute numbers and percentages. Classical parametric and non-parametric statistical tests will be used to compare differences between the intervention and control groups as appropriate.

PPV will be calculated with 95% confidence intervals (CI) and used for statistical testing and comparison between groups. This comparison will be performed primarily on the total number of patients included, but adjustments for the temporal inclusion design using hierarchical models will also be explored. The stepped wedge design allows for investigation into potential temporal trends, and subgroup analysis will be done to compare PPV (CI) for the various clusters and time periods using appropriate linear and non-linear curve fitting models.

A modified Rankin Scale (mRS) shift analysis to assess discharge and 90-day functional outcomes [25] will be performed. mRS will be analysed both as an ordinal scale (0–6) and as a dichotomised variable where mRS 0-2 defines a favourable outcome. As shown in Table 2, a certain analysis will only be considered for a subgroup population.

Statistical analysis will be performed in Stata and R.

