### Trial status

This manuscript is based on ParaNASPP protocol version 1, January 10, 2019. The study protocol is available at ClinicalTrials.gov (NCT04137874). Amendments to the protocol will be published here. The ParaNASPP study started inclusions in the control group on June 3, 2019. At the time of submitting this manuscript (June 2021), we are still recruiting. Five ambulance stations in Oslo and the SU at OUH are participating. The active recruitment of patients ends July 1, 2021. The data collection will be finished approximately October 1, 2021, when the final 90-day follow-up is complete. Submission of this paper has been delayed. As COVID-19 hit during spring 2020 concern from the hospital administration made us temporarily pause data inclusion from March 2020 to October 2020, lasting for almost seven months. The pandemic affected and delayed the project team as we were involved in urgent clinical duties, as was the case for our collaborators and this further challenged the progress that we wanted. The pandemic also brought on the need for changing the preintervention training method.

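### The primary PPV test pools all patients without period or station, so about half of any calendar trend enters the intervention effect and the 5% error rate is not held

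*Protocol article*

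**What the plan says.** The Statistics section of the protocol article sets the order for the primary outcome: "This comparison will be performed primarily on the total number of patients included, but adjustments for the temporal inclusion design using hierarchical models". The second kind of analysis is named there only as an exploratory addition. Stations and periods otherwise enter through a secondary look: "subgroup analysis will be done to compare PPV (CI) for the various clusters and time periods". For outcomes in general it states: "Classical parametric and non-parametric statistical tests will be used to compare differences between the intervention and control groups as appropriate".

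The Study design section describes the wedge. After 12 weeks with every station in control, "a random and sequential crossover of clusters from control to intervention will take place until all clusters are activated for intervention". The Sample size calculation section gives six 12-week periods and a planned 1300 patients, and derives its minimum as follows: "We used a two-sided test with alpha 5% and beta 80% and need a total of 808 patients". Trial status adds that the pandemic made the team "temporarily pause data inclusion from March 2020 to October 2020, lasting for almost seven months". The section on preintervention training says that training became digital between activation of clusters three and four.

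**The concern.** The word *but* in the Statistics section sets the total-patient comparison against the time-adjusted models. The primary comparison is therefore unadjusted, and the phrase does not merely name an analysis set.

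Randomising the order of stations does not balance calendar time between arms in a stepped wedge: control patients come early and intervention patients late. Only adjustment for period separates the two. There are two distinct defects:

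- **Bias.** Any change in case mix, referral or physician acceptance over time enters the crude contrast. A documented break in inclusion during the pandemic makes such a change plausible.
- **Standard error.** A binomial standard error ignores that patients of one station may resemble each other, and stations contribute unequally to the two arms.

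At stake is whether a significant PPV difference can be attributed to the ParaNASPP model, and whether a null result can be believed.

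**Working it through.** **1. The planned sample size.** Inputs: 40% versus 50%, two-sided 5%, 80% power, 1:1.

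- Uncorrected, per arm: [1.96·√(2·0.45·0.55) + 0.8416·√(0.24 + 0.25)]² / 0.10² = 387.3, so 388 per arm and 776 in total.
- With continuity correction, per arm: (387.3/4)·[1 + √(1 + 4/(387.3·0.10))]² ≈ 407.1, so 816 in total.

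The stated 808 lies within 1% of 816. It is a two-proportion size with no term for station or period, which fits a pooled primary test.

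**2. Calendar imbalance.** Assume five stations of equal size and six periods. Control station-periods number 5, 4, 3, 2, 1, 0 and intervention 0, 1, 2, 3, 4, 5.

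- Mean period, control: (5 + 8 + 9 + 8 + 5)/15 = 35/15 = 2.33.
- Mean period, intervention: (2 + 6 + 12 + 20 + 30)/15 = 70/15 = 4.67.

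The pooled difference absorbs 2.33 times the change per period, which is 2.33/5 = 47% of a linear change from period 1 to period 6.

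**3. The pandemic pause.** Inclusion began on 3 June 2019, so March 2020 is study week 38.9 to 43.1, inside scheduled period 4 (weeks 36–48).

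- Control exposure before the pause: (12 + 2·0.238)/15 = 83% to (12 + 2·0.595)/15 = 88%.
- Intervention exposure before it: (3 + 3·0.238)/15 = 25% to (3 + 3·0.595)/15 = 32%.

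For a shift at week 40 the shares are 12.67/15 = 84.4% and 4/15 = 26.7%. The pooled contrast then absorbs 57.8% of the shift, so a 10-point shift gives 5.8 points.

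The schedule is only approximate. From 3 June 2019 to 1 July 2021 is 108.4 weeks; less seven months (30.4 weeks) this leaves about 78 weeks, not 72. If the shift falls before period 5 the absorbed share is 53%; before period 4 it is 60%.

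**4. Ignoring station, no trend.** Station shares of the two arms differ by 4/15, 2/15, 0, −2/15 and −4/15; the squares sum to 40/225 = 0.178. With 650 patients per arm, true variance over binomial variance is (1 − ICC) + ICC·0.178·650/2.

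- ICC 0.01: 0.99 + 0.578 = 1.568. The rejection rate is P(|Z| > 1.96/√1.568) = 12%.
- ICC 0.05: 0.95 + 2.889 = 3.839. The rejection rate is 32%.

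**5. Type I error of the pooled test**, 1300 patients, no intervention effect, from simulation and normal approximation:

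| Assumed scenario | False effect (points) | Rejection |
|---|---|---|
| No trend, ICC 0 | 0 | 5% |
| No trend, ICC 0.01 | 0 | 11–12% |
| No trend, ICC 0.05 | 0 | 32–34% |
| 1 point per period, ICC 0 | 2.3 | 13–14% |
| 2 points per period, ICC 0 | 4.7 | 39–40% |
| 5-point shift at week 40, ICC 0 | 2.9 | 18% |
| 10-point shift at week 40, ICC 0 | 5.8 | 55–57% |

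**6. The adjusted analysis.** In simulations at ICC 0.01 with period and station in the model, the mean estimate stayed within 0.2 points of zero and rejection was 4.5–5.2% in every trend scenario. These runs contained no station-by-period variation.

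Precision follows from the Hussey–Hughes variance with 43.3 patients per cell and mean PPV 0.45. At ICC 0.01, σ² = 0.99·0.2475/43.3 = 0.00565 and τ² = 0.002475. The variance is 5σ²(σ² + 6τ²)/(20σ² + 70τ²) = 0.00202, so SE = 4.5 points. The pooled test's nominal SE is √(0.2475·2/650) = 2.8 points (2.7 at PPV 0.42).

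| ICC | Power for 10 points, N = 808 | N = 1300 | N for 80% power |
|---|---|---|---|
| 0 | 55% | 75% | about 1460 |
| 0.01 | 44% | 60% | about 2190 |
| 0.05 | 40% | 56% | about 2310 |

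**The case against.** The plan does not overlook time and station. It foresees hierarchical models and PPV by cluster and period, so a conflict with the pooled result would become visible. That is fair, but these analyses rank below the primary test. They do not protect its p-value, and the article gives no rule for the case that they disagree.

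Only about half of a trend enters the estimate, and its sign is open. This stands, and the figures here reflect it.

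The larger error rates rest on assumed values. The article gives no ICC, trend or shift. A 10-point shift equals the whole target effect, and an ICC of 0.05 may be high for stations in one city that deliver to one stroke team. This stands too: those rows are illustrations. The bias per unit of trend follows from the design alone, given equal stations.

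For the secondary outcomes, the sentence on classical tests is generic and leaves room for judgement, and a separate analysis plan may specify models. This part is therefore weaker, and the conclusion does not need it.

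An unseen analysis plan could add model detail. To make the adjusted model primary, though, it would have to reverse an order that the article states.

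**Conclusion.** The concern holds. The stated primary analysis is biased by any calendar trend and does not hold its 5% level when stations differ. From the design alone, with equal stations, it absorbs 47% of a linear change across the six periods. It absorbs 53–60% of a shift at the pause, depending on where the pause falls in the schedule.

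A drift of 1 to 2 points per period would produce about a quarter to a half of the 10-point target with no true effect; a decline would mask a true effect by as much. Even without a trend, an assumed ICC of 0.01 roughly doubles the type I error at 1300 patients. This must be corrected, because the trial's main conclusion rests on it.

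**What to change.** Reverse the order of the two analyses.

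- **Primary analysis:** a mixed model for stroke versus non-stroke with an intervention indicator, fixed calendar-period effects and random station and station-by-period effects. Define periods by actual dates, and split the period in which the pause fell.
- **Inference for five stations:** a permutation test over the 5! = 120 possible station orders, which matches the lottery used, or a small-sample correction.
- **Pooled PPVs:** report them with intervals as description only.
- **Secondary between-group comparisons:** state that they carry the same period and station terms.
- **Power:** restate it on the new primary model, with an explicit ICC range.

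The change needs wording and some programming, but no new data. The real cost is precision: SE about 4.5 points at ICC 0.01 instead of a nominal 2.7–2.8, and power of about 56–75% at 1300 patients for ICC 0–0.05. A station-by-period term lowers it further. With an assumed cluster autocorrelation of 0.5–0.8, power is about 57–58% at ICC 0.01 and 34–43% at ICC 0.05, before any small-sample penalty. The pooled test's apparent advantage is not real precision.

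The article does not show whether data were already locked or compared. The change should be dated and made before any comparison by arm; if that is no longer possible, it should be reported as made afterwards.
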